### (3)Allocation

Participants will be first recruited from the Huzhou University campus by blinded research assistants. We expect the possible recruitment rate to be 60%–70%.

Version number2.0 ; Dated 15thFeb. 2022

If the number of participants is not enough, we will recruit the remaining participants from the campus of Huzhou University by setting up recruitment stations, sending flyers, posting posters, and university social pages. Volunteers can consult their family or primary doctor before making a decision. Volunteers can also ask questions about the research project and the researcher will further explain and answer the question until volunteers understand it. If volunteers voluntarily participate in this study, volunteers can still withdraw from the study at any time without any impact on their rights.

In addition, this study involved multiple test items. The principal investigator will invite 3 assistants from the School of Physical Education of Huzhou University, who are teachers with more than 5 years of experience in exercise science experiments, to assist in the testing and evaluation of this study. To avoid bias and ensure effective data collection, Reliability will be assessed by calculating the intraclass correlation coefficient (ICC) with 95% confidence intervals. ICC can be used with quantitative data organized into groups, and it measures the consistency of values across cases. Comparing the results of the assistant, if the ICC value is greater than 0.9, it means that the reliability is good, and the results can be used.

Assistants will review the consent form with participants; upon signing, participants began data collection procedures. All data collection will occur in private offices on the Huzhou University campus. Participants will attend consent signing and data collection at individual times to prevent overlap and ensure participant privacy. Trained assistants will conduct data collection which will take place between March 2022 and July 2022.

### **3.3 Experiment content and test sequence**

#### **3.3.1 Experiment content**

Participants will be asked to completely relax and sit comfortably in two quiet and bright rooms with an ambient temperature set at 24°C, located in the Sports Anatomy and Physiology Laboratory and the Laboratory of Cognitive Neuroscience and Learning Sciences of Huzhou University. All tests will be performed in the Sports Anatomy and Physiology Laboratory, except for rs-EEG tests in the Cognitive

Neuroscience and Learning Sciences Laboratory.

The Experiment contents of this study will be expected to include four parts, as follows:

(1) Mental Health questionnaires. This study will include Depression Status Inventory (DSI; Zung 1965) and State-Trait Anxiety Inventory Version (STAI; Spielberger et al., 1983).

(2) Cognitive Performance measurement. This study will use Stroop color word test (Eprime 2.0 Professional, Psychology SoftwareTools, Inc., Pittsburgh, PA). SCWT is widely applied to measure cognitive function by researchers and clinicians (MacLeod, 1991, 2015; Swanson, 2005). Stroop designed a classic test experiment, in which using different colors of ink to print color names in 1935. For example, if you see the word "red" printed with blue ink and say "blue", this will cause cognition interference (MacLeod, 1991). The Stroop effect appears when the individual's response time is prolonged due to the targeted selection of attention or the individual cannot inhibit the brain's first response to autonomous reading (MacLeod, 2015). The theoretical explanation of the Stroop effect includes automatic and processing speed (MacLeod, 1991). The relative speed of processing shows that humans can read written words faster than recognize colors, and that speed conflicts can cause interference (MacLeod, 2015). Automaticity is the automatic process that takes place quickly, unconsciously and effortlessly (Sahinoglu & Dogan, 2016). Barnett believed that because the name of the color conflicts with the process of automatically reading words, more attention may be required when recognizing the color of a word (Barnett et al., 2020).

(3) Physical Fitness measurement. This study will include PF test and body scale (Huawei Smart Scale 3 Pro, Huawei, China). The indexes of PF are including: Height and Weight (Weight scale, Jiangsu Suhong Medical Equipment Co., Ltd., China), Cardiopulmonary function (JH-1662 Electronic Spirometer, Jiangsu Suhong Medical Equipment Co., Ltd., China), Muscle strength (JH-1881 Electronic Grip , Changzhou Jihao Electronics Co., Ltd., China), Flexibility (Mechanical flexionr, Jiangsu Suhong Medical Equipment Co., Ltd., China), Balance (One-leg standing test Version number2.0 ; Dated 15thFeb. 2022

with eyes closed), Power of lower limbs (Simple long jump mat., Jiangsu Suhong Medical Equipment Co., Ltd., China). The indexes of body composition include: Body water, Protein level, Body fat, Muscle mass, Bone mineral content (Huawei Smart Scale 3 Pro, Huawei, China).

(4) Physiological data acquisition. This study will include HRV measurement (uBioMacpa v70, BioSense Creative, Korea) and rsEEG measurement (actiCHamp Plus, Brain Products GmbH, Gilching, Germany).

### **3.3.2 Test sequence**

Following informed consent.

In the 1st study, all participants in TC exercise group will be assessed before and after a 45-minutes TC training session in 4th week to determine the effects of single TC training session. Both pre-test2 and post-test1 will be in the following order: 1)SCWT, and 2) HRV test.

In the 2nd study, all participants in both TC exercise group and control group will be assessed before and after 12-weeks to evaluate the long-term effects of TC training session. Both pre-test1 and post-test2 will be in the following order: 1)DSI and STAI, 2) SCWT, 3)HRV test, 4)PF test and Body Scale, and 5)rs-EEG.

## **3.4 Experimental apparatus, procedure, and measure assessment**

### **3.4.1 Depression Status Inventory**

The state of depression can be measured by Depression Status Inventory (DSI; Zung 1965), DSI consists of 20 items, and each item has four answers, in which it is assigned 1 to 4 points according to the time level. Total scores of all items range from 20 to 80, and lower scores represent a "lower state of depression" (Kim et al., 2004). Compared to the clinical judgment of a psychiatrist, the reliability of the DSI was 0.90, the specificity of the DSI was 0.80, and the sensitivity of the DSI was 0.90 (Alber et al., 1992).

DSI is a short-term evaluation scale and questionnaire for others. It is convenient to operate and easy to grasp. It can effectively reflect the symptoms of  
Version number2.0 ; Dated 15thFeb. 2022

depression and their severity and changes. It is especially suitable for general hospitals to find depression patients. If the subject has a low level of education or intelligence and cannot perform self-assessment, DIS can be used to evaluate the examiner. DIS has been widely used abroad. Mainland of China was translated into Chinese in 1985 and was first used to evaluate the efficacy of the antidepressant minaprine in the treatment of depression and clinical research on depression.

Scoring method: Each item is scored on four levels of 1, 2, 3, and 4. There are a total of 20 items, which reflect the four groups of specific symptoms of depression: Psychic-emotional symptoms, including two items of depression and crying; Physical disorders: eight items including day-to-day differences in mood, sleep disorders, constipation, appetite loss, libido loss, fatigue, weight loss and tachycardia; Psychomotor disorder, including psychomotor retardation and agitation; Psychological disorders of depression, including confusion, hopelessness, irritability, indecision, self-devaluation, feeling of emptiness, suicidal thinking and dissatisfaction, a total of eight items. In these 20 items, 10 items are set in positive words, which are scored in reverse order, and the remaining 10 items are negative words that should be scored in the order of 1-4 above. The scores range from 25 to 100, normal scores range from 25 to 49, Mildly Depressed scores range from 50 to 59, Moderately Depressed scores range from 60 to 69, and Severely Depressed scores are 70 and above.

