## **3.6 Statistical analysis**

The sample's demographic characteristics, descriptive data, age, education, race, and ethnicity will be described using the mean and standard deviation or frequencies and proportions as appropriate.

In the 1st study, based on the results of the pre-test and post-test in only TC exercise group, both Paired t-test and McNemar test will be used to explore differences in the outcomes that are response time and error ratio in SCWT, and LF, HF, LF/HF, Mean BPM, SDNN and RMSSD in HRV test.

In the 2nd study, there will also be three levels of outcomes in both TC exercise  
Version number 2.0 ; Dated 15thFeb. 2022

group and control group. The primary outcomes are response time and error ratio in SCWT; LF, HF, LF/HF, Mean BPM, SDNN and RMSSD in HRV test; Average power in EEG. The secondary outcomes are body fat, BMI, body fat ratio in body composition; and vital capacity, balance, handgrip strength, vertical jump, and sit and reach flexibility in PF. And the tertiary outcomes are depression and anxiety on psychological scales. Two-way repeated measures ANOVA will be performed with 2 levels in the group factor (Group: TC, Control) and 2 levels in the time factor (Time: pre-test1, post-test2) to assess three levels of outcomes. All analyses will be conducted with IBM SPSS 26.0, with the statistical significance level set at  $p \leq 0.05$ .

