| 12. I find it easy to do the things I used to. | 4                       | 3                   | 2                             | 1                   |
| 13. I am restless and can't keep still.        | 1                       | 2                   | 3                             | 4                   |

|                                                            |   |   |   |   |
|------------------------------------------------------------|---|---|---|---|
| 14. I feel hopeful about the future.                       | 4 | 3 | 2 | 1 |
| 15. I am more irritable than usual.                        | 1 | 2 | 3 | 4 |
| 16. I find it easy to make decisions.                      | 4 | 3 | 2 | 1 |
| 17. I feel that I am useful and needed.                    | 4 | 3 | 2 | 1 |
| 18. My life is pretty full.                                | 4 | 3 | 2 | 1 |
| 19. I feel that others would be better off if I were dead. | 1 | 2 | 3 | 4 |
| 20. I still enjoy the things I used to do.                 | 4 | 3 | 2 | 1 |

Add up all of the numbers that were circled and consult the scale provided below:

The scores range from 25-100. TM

25-49 Normal Range TM

50-59 Mildly Depressed TM

60-69 Moderately Depressed TM

70 and above Severely Depressed

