## Appendix C (Chinese Version)

### 抑郁状态问卷(DSI)

编号: \_\_\_\_\_ 性别: ☐ 男 ☐ 女

年龄: \_\_\_\_\_岁

指导语: DSI 由 20 个陈述句和相应问题条目的组成, 请被测试者根据最近一周的情况, 对每一个条目均按 1、2、3、4 四级给予评分, 请如实回答以下 20 项症状。

| 题目                                       | 偶尔或无  | 有时 | 经常 | 持续 |
|------------------------------------------|-------|----|----|----|
|                                          | 打勾(√) |    |    |    |
| 1. 你感到情绪沮丧, 郁闷吗?                         | 1     | 2  | 3  | 4  |
| 2. 你要哭或想哭吗?                              | 4     | 3  | 2  | 1  |
| 3. 你感到早晨心情最好吗?                           | 1     | 2  | 3  | 4  |
| 4. 你夜间睡眠不好吗?经常早醒吗?                       | 1     | 2  | 3  | 4  |
| 5. 你吃饭象平时一样多吗?食欲如何?                      | 4     | 3  | 2  | 1  |
| 6. 你感到体重减轻了吗?                            | 4     | 3  | 2  | 1  |
| 7. 你的性功能正常吗?乐意注意具有吸引力的异性, 并好和他/她在一起、说话吗? | 1     | 2  | 3  | 4  |
| 8. 你为便秘烦恼吗?                              | 1     | 2  | 3  | 4  |
| 9. 你的心跳比平时快吗?                            | 1     | 2  | 3  | 4  |
| 10. 你无故感到疲劳吗?                            | 1     | 2  | 3  | 4  |
| 11. 你坐卧不安, 难以保持平静吗?                      | 4     | 3  | 2  | 1  |
| 12. 你做事情比平时慢吗?                           | 4     | 3  | 2  | 1  |
| 13. 你的头脑象往常一样清楚吗?                        | 1     | 2  | 3  | 4  |

|                        |   |   |   |   |
|------------------------|---|---|---|---|
| 14. 你感到生活很空虚吗?         | 4 | 3 | 2 | 1 |
| 15. 你对未来感到有希望吗?        | 1 | 2 | 3 | 4 |
| 16. 你觉得决定什么事很容易吗?      | 4 | 3 | 2 | 1 |
| 17. 你比平时更容易激怒吗?        | 4 | 3 | 2 | 1 |
| 18. 你仍旧喜爱自己平时喜爱的事情吗?   | 4 | 3 | 2 | 1 |
| 19. 你感到自己是有用的和不可缺少的人吗? | 1 | 2 | 3 | 4 |
| 20. 你曾经想过自杀吗?          | 4 | 3 | 2 | 1 |

注:1972年 Zung 氏增编了与自评抑郁量表(Self-Rating Depression Scale, SDS)相应的检查者用本,改自评为他评,称为抑郁状态问卷(Depression Status Inventory, DSI)。评定时间跨度为最近一周。DSI 由 20 个陈述句和相应问题条目的组成。每一条目相当于一个有关症状,按 1-4 级评分。

评分方法:每一个条目均按 1、2、3、4 四级评分。20 个条目中有 10 项(第 2、5、6、11、12、14、16、17、18 和 20)是用正性词陈述的,为反序计分,其余 10 项是用负性词陈述的,按上述 1-4 顺序评分。

条目反映抑郁状态四组特异性症状:

1. 精神性——情感症状,包含抑郁心境和哭泣两个条目;
2. 躯体性障碍:包含情绪的日间差异、睡眠障碍、食欲减退、性欲减退、体重减轻、便秘、心动过速、易疲劳共八个条目;
3. 精神运动性障碍,包含精神运动性迟滞和激越两个条目;
4. 抑郁的心理障碍,包含思维混乱、无望感、易激惹、犹豫不决、自我贬值、空虚感、反复思考自杀和不满足,共八个条目。

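### The Chinese DSI form reorders the items but keeps the English reverse-scored positions, so 12 of 20 items, including the suicide item, are scored backwards and the total is not a valid depression score

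*Protocol*

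**What the plan says.** Section 3.4.1 describes the DSI as 20 items scored 1 to 4, with lower totals meaning less depression. On reverse scoring it states: "In these 20 items, 10 items are set in positive words, which are scored in reverse order". Suicidal thinking is one of the listed symptoms: "self-devaluation, feeling of emptiness, suicidal thinking and dissatisfaction, a total of eight items".

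Appendix C prints two forms. The English form reverses items 2, 5, 6, 11, 12, 14, 16, 17, 18 and 20. Its suicide item is number 19 ("I feel that others would be better off if I were dead"), keyed forward. The Chinese form puts the items in another order, and its suicide question is number 20. Its scoring note gives the same ten item numbers and says they are positively worded and reverse-scored; the list ends "17、18 和 20)是用正性词陈述的,为反序计分". Its table prints the same ten positions as 4-3-2-1.

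Section 3.4.1 also gives two ranges. One is "Total scores of all items range from 20 to 80"; the other is 25 to 100, with severity bands starting at 50, 60 and 70. The English form says "Add up all of the numbers that were circled and consult the scale provided below", and the scale it points to is the 25 to 100 one.

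In section 3.6, "the tertiary outcomes are depression and anxiety on psychological scales", compared between groups over time by a repeated-measures ANOVA. Sections 3.1 and 3.3.2 place the DSI in the assessments shortly before and shortly after the 12 weeks. Section 3.5.4 has adverse events recorded during the intervention.

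**The concern.** A key that belongs to one item order has been applied to another. Items meant to be reversed are scored forward, and negatively worded items are reversed. Depression is a named outcome and part of Hypothesis 2. If more than half of its items are summed with the wrong sign, the total mixes correctly scored symptoms with inverted ones, and no analysis model can repair that.

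The suicide item adds a safety side. Under the printed Chinese key the most serious answer gets the score that should mean no problem, so anyone who looks only at item scores or totals would be misled. The visible protocol does not say who looks at that answer, when, or what follows.

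**Working it through.** **Inputs.** Item wording and printed keys come from Appendix C, English and Chinese. The direction of the scale comes from section 3.4.1. A positively worded item should run 4-3-2-1 from the lowest to the highest frequency category; a negatively worded one should run 1-2-3-4.

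**English form, as a check on the stated count.** Ten items are reversed, all ten are positively worded, and none is miskeyed. The figure of 10 in section 3.4.1 is reproduced for this form.

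**Chinese form, item by item.**

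- Negative wording, forward key (right): 1 low mood, 4 poor sleep, 8 constipation, 9 fast heartbeat, 10 fatigue.
- Positive wording, reversed key (right): 5 appetite, 16 decisions, 18 enjoyment.
- Negative wording, reversed key (backwards): 2 crying, 6 weight loss, 11 restlessness, 12 slowness, 14 emptiness, 17 irritability, 20 suicide.
- Positive wording, forward key (backwards): 3 best mood in the morning, 7 sexual function, 13 clear mind, 15 hope, 19 usefulness.

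Correctly keyed: 5 + 3 = 8. Backwards: 7 + 5 = 12. Positive by wording: 3 + 5 = 8, not 10.

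**Effect on the total.** Suppose every item has the same severity x, from 1 (best) to 4 (worst). The correct total is 20x. The printed key gives 8x + 12(5 − x) = 60 − 4x.

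| x | Correct total | Printed-key total |
|---|---|---|
| 1 | 20 | 56 |
| 2 | 40 | 52 |
| 3 | 60 | 48 |
| 4 | 80 | 44 |

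**Effect on a change.** Let A be the summed improvement on the 8 correctly keyed items and B that on the 12 miskeyed ones. The correct total changes by −(A + B); the printed total changes by −A + B.

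- One point better on every item: A = 8 and B = 12, so the correct change is −20 and the printed change is +4.
- One point better on the 8 correctly keyed items only: A = 8 and B = 0, so both changes are −8.
- A and B equal: the printed change is 0, whatever the true benefit.

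The sign therefore reverses when B exceeds A. In averages per item this happens when improvement on the 12 exceeds 8/12, or two-thirds, of the improvement on the 8.

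**Range.** Twenty items scored 1 to 4 sum to 20 to 80, so a raw sum cannot span 25 to 100. The protocol gives no conversion. A linear mapping would be × 1.25 (25/20 = 100/80 = 1.25), which puts the bands at raw 40, 48 and 56. This mapping is an assumption.

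**Timing against section 3.5.4.** One DSI sitting comes before training starts and the other after it ends, so neither lies in the recording period. Section 1.2 mentions a fourth-week follow-up under the second study, but the only week-4 test described, in section 3.3.2, is the Stroop test and HRV in the tai chi group. Section 1.2 is not fully reconciled with this, and the flow diagram is not shown.

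**The case against.** The count of 12 cannot be put down to a damaged table, because the Chinese prose note lists the same ten numbers, including 20. Other objections carry more weight.

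- **Which form is used.** The protocol does not say. Recruitment on a Chinese campus, Chinese Stroop stimuli and an appended Chinese version make it very likely, but it remains an inference.
- **Benefit shown as harm.** A reader might infer that any real benefit of tai chi would appear as harm. The protocol does not support that. The reversal needs the 12 miskeyed items together to change more than the 8 correct ones, and the 8 include low mood, sleep, fatigue and enjoyment.
- **Severity labels.** A reader might set 44 and 56 against the bands and conclude that the most depressed respondent is labelled normal. The instruction to read a sum against bands is printed only on the English form; the Chinese form shows no bands, and section 3.6 plans no analysis by severity category.
- **Missed disclosures.** A reader might infer that a suicidal answer would go unseen. That requires self-completion followed by review of scores alone. The mode is unclear: section 3.4.1 describes a scale for rating others and the Chinese note calls it examiner-rated, but the Chinese instruction asks the respondent to rate the past week ("请被测试者根据最近一周的情况"). An examiner would hear the answer, and on paper the tick sits under its category heading.
- **Silence on handling.** The removed consent pages may set a procedure. The injuries named in section 3.5.4 are examples, not a closed list, and that section also requires prompt reporting of adverse events to the ethics committee.

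These objections limit the size of the effect and make the safety part secondary. They leave the key error intact.

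**Conclusion.** The scoring key on the Chinese form is wrong as printed: 12 of 20 items run backwards, including the suicide item. The resulting total is not a valid depression score. With equal change on all items it reverses direction and shrinks to one-fifth of the true size (+4 against −20); with other symptom profiles it may keep the right sign or show nothing. This rests on one inference, that participants complete the Chinese form. The two score ranges in section 3.4.1 are also unreconciled, which is a smaller matter because the planned analysis does not use the bands.

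The handling of the suicide item is a secondary point. The visible text sets no action on that answer, and both sittings fall outside the recording period of section 3.5.4. Whether a procedure exists elsewhere cannot be judged from what is shown.

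**What to change.** 1. On the Chinese form, reverse only items 3, 5, 7, 13, 15, 16, 18 and 19, and score the other twelve, including item 20, from 1 to 4. Change the count of 10 to 8 for this form in section 3.4.1 and in the Chinese note, and correct the item list there.
2. Rescore any answers already held as ticked categories. If only item scores were stored under the printed key, replace each of the 12 miskeyed scores by 5 minus itself. Stored totals alone cannot be repaired.
3. State one range in section 3.4.1. The simplest choice is the raw 20 to 80 total for analysis. If the 25 to 100 bands are to be reported, state the conversion.
4. Run the recording period of section 3.5.4 from consent to the last assessment. At both sittings and in both arms, have the ticked category of the suicide item, not its score, seen before the participant leaves, and refer a current disclosure to an existing service. Check that the consent information agrees.

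The cost is small. It comes to a form amendment with ethics approval, brief instruction of the assistants, and care over confidentiality, since the assistants are teachers at the participants' university. No visit is added: participants attend individually, and the questionnaires come first in the test order.

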### **3.4.2 State-Trait Anxiety Inventory**

This study will use State-Trait Anxiety Inventory Version (STAI; Spielberger et al., 1983) to analyze the anxiety characteristics of college students. The first edition (STAI-Form X) came out in 1970 and has conducted 2,000 studies involving medicine, education, psychology and other sciences. The author revised STAI-Form X in 1979 and the 1980 revision (STAI-Form Y) began to apply. The former describes unpleasant emotional experiences, such as fear, tension, nervousness, and anxiety, accompanied by hyperactivity of the autonomic nervous system, but this is usually short-lived. Trait anxiety is used to describe a relatively stable anxiety Version number 2.0 ; Dated 15thFeb. 2022

tendency, and this tendency is a unique trait of each person. Spielberg compiled the STAI, which provides internal scientists, behaviorists, and clinicians with a tool to distinguish between transient emotional states of anxiety and personality trait anxiety tendencies for clinical practice services and different research purposes.

STAI consists of 40 descriptive questions in the guide and two subscales. Items 1-20 are the State Anxiety Inventory (STAI, Form YI, hereinafter referred to as S-AD. Half of the items describe negative emotions, and the others are positive emotions. Mainly used to evaluate immediate or present specific experiences, or feelings in situations such as tension, worry, fear, and neuroticism. It can be used to evaluate state anxiety under stress conditions. The 21-40 topic is the Trait Anxiety Inventory (STAI, Form YI, T-AI), which is used to assess individual frequent emotional experiences. Among them, 11 items are items describing negative emotions and 9 items are positive emotion items. It can be widely used to assess the anxiety of internal medicine, surgery, psychosomatic diseases and mental patients; it can also be used for screening. Anxiety issues of college students, military personnel, and other professional groups; and evaluation of the effects of psychotherapy and medication. The questionnaire can be used for individual or group testing, and the subjects generally only need a junior high school education level. Subjects can circle the answers based on self-assessment or self-report. There is no time limit for the entire questionnaire process. The scale includes item content explicitly assessing worry and bothersome thoughts, as well as physical problems such as restlessness, suggesting that it is a strong overall measure of GAD severity. Internal consistencies across the three study waves were 0.887, 0.912, and 0.917 (Newman et al., 2020).

The reliability of STAI tested among college students is 0.850. In addition, the construct validity of the STAI, the correlation between items (KMO) score is 0.824 ( $>0.30$ ) and  $p=0.000$ . Where, the State showed  $KMO=0.818$ ,  $p=0.000$ , and Cronbach alpha found 0.797; Trait showed  $KMO=0.783$ ,  $p=0.000$ , and Cronbach alpha found 0.781 (Vitasari et al., 2011).

Generally speaking, the entire questionnaire can be completed in about 15 minutes. Each item of STAI is scored from grade 1 to grade 4. In S-AI, 1 means not at

Version number 2.0 ; Dated 15th Feb. 2022

all, 2 means some, 3 means moderate, and 4 means very obvious. In T-AI, 1 means almost none, 2 means some, 3 means often, 4 means almost always. The subjects choose the most suitable score based on their own experience. All positive emotion items are scored in reverse order. Calculate the cumulative scores of the S-AI and T-AI scales, with a minimum of 20 and a maximum of 80, reflecting the degree of state or trait anxiety (Hui, 2020).

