#### STAI Form Y-1

DIRECTIONS: A number of statements which people have used to describe themselves are given below. Read each statement and then circle the appropriate number to the right of the statement to indicate how you feel right now, that is, at this moment. There are no right or wrong answers. Do not spend too much time on any one statement but give the answer which seems to describe your present feelings best.

| Topic                                                 | Not at
all  | Somewhat | Moderately
so | Very
much so |
|-------------------------------------------------------|----------------|----------|------------------|-----------------|
|                                                       | Please tick(✓) |          |                  |                 |
| 1. I feel calm.                                       | 1              | 2        | 3                | 4               |
| 2. I feel secure.                                     | 4              | 3        | 2                | 1               |
| 3. I am tense.                                        | 1              | 2        | 3                | 4               |
| 4. I feel strained.                                   | 1              | 2        | 3                | 4               |
| 5. I feel at ease.                                    | 4              | 3        | 2                | 1               |
| 6. I feel upset.                                      | 1              | 2        | 3                | 4               |
| 7. I am presently worrying over possible misfortunes. | 1              | 2        | 3                | 4               |
| 8. I feel satisfied.                                  | 4              | 3        | 2                | 1               |
| 9. I feel frightened.                                 | 1              | 2        | 3                | 4               |
| 10. I feel comfortable.                               | 4              | 3        | 2                | 1               |

|                            |   |   |   |   |
|----------------------------|---|---|---|---|
| 11. I feel self-confident. | 4 | 3 | 2 | 1 |
| 12. I feel nervous.        | 1 | 2 | 3 | 4 |
| 13. I am jittery.          | 1 | 2 | 3 | 4 |
| 14. I feel indecisive.     | 1 | 2 | 3 | 4 |
| 15. I am relaxed.          | 4 | 3 | 2 | 1 |
| 16. I feel content.        | 4 | 3 | 2 | 1 |
| 17. I am worried.          | 1 | 2 | 3 | 4 |
| 18. I feel confused.       | 1 | 2 | 3 | 4 |

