### STAI Form Y-2

**DIRECTIONS:** A number of statements which people have used to describe themselves are given below. Read each statement and then circle the appropriate number to the right of the statement to indicate how you generally feel. There are no right or wrong answers. Do not spend too much time on any one statement but give the answer which seems to describe how you generally feel.

| Topic                                    | Not at
all  | Somew
hat | Moderat
ely so | Very
much
so |
|------------------------------------------|----------------|--------------|-------------------|--------------------|
|                                          | Please tick(✓) |              |                   |                    |
| 21. I feel pleasant.                     | 1              | 2            | 3                 | 4                  |
| 22. I feel nervous and restless.         | 1              | 2            | 3                 | 4                  |
| 23. I feel satisfied with myself.        | 4              | 3            | 2                 | 1                  |
| 24. I wish I could be as happy as others | 4              | 3            | 2                 | 1                  |

|                                                                                              |   |   |   |   |
|----------------------------------------------------------------------------------------------|---|---|---|---|
| seem to be.                                                                                  |   |   |   |   |
| 25. I feel like a failure.                                                                   | 1 | 2 | 3 | 4 |
| 26. I feel rested.                                                                           | 4 | 3 | 2 | 1 |
| 27. I am “calm, cool, and collected”                                                         | 4 | 3 | 2 | 1 |
| 28. I feel that difficulties are piling up so that I cannot overcome them.                   | 1 | 2 | 3 | 4 |
| 29. I worry too much over something that really doesn't matter.                              | 1 | 2 | 3 | 4 |
| 30. I am happy .                                                                             | 4 | 3 | 2 | 1 |
| 30. I have disturbing thoughts.                                                              | 1 | 2 | 3 | 4 |
| 31. I lack self-confidence.                                                                  | 1 | 2 | 3 | 4 |

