### 特质焦虑问卷

指导语：下面列出的是人们常常用来描述他们自己的一些陈述，请阅读每一个陈述后，然后在右边恰当约圈内打勾，来表示你经常的感觉。没有对或错的回答。不要对任何一个陈述花太多的时间去考虑，但所给均回答应该是你平常所感觉到的。

| 题目              | 完全
没有 | 有些 | 中等
程度 | 非常
明显 |
|-----------------|----------|----|----------|----------|
|                 | 打勾(√)    |    |          |          |
| 21. 我感到愉快       | 1        | 2  | 3        | 4        |
| 22. 感到神经过敏和不安   | 1        | 2  | 3        | 4        |
| 23. 我感到自我满足     | 4        | 3  | 2        | 1        |
| 24. 我希望能象别人那样高兴 | 4        | 3  | 2        | 1        |

|                               |   |   |   |   |
|-------------------------------|---|---|---|---|
| 25. 我感到我象衰竭一样                 | 1 | 2 | 3 | 4 |
| 26. 我感到很宁静                    | 4 | 3 | 2 | 1 |
| 27. 我是平静的、冷静的和泰然自若的           | 4 | 3 | 2 | 1 |
| 28. 我感到困难一一堆集起来，因此无法克服        | 1 | 2 | 3 | 4 |
| 29. 我过分忧虑一些事，实际这些事无关紧要        | 1 | 2 | 3 | 4 |
| 30. 我是高兴的                     | 4 | 3 | 2 | 1 |
| 31. 我的思想处于混乱状态                | 1 | 2 | 3 | 4 |
| 32. 我缺乏自信心                    | 1 | 2 | 3 | 4 |
| 33. 我感到安全                     | 4 | 3 | 2 | 1 |
| 34. 我容易做出决断                   | 4 | 3 | 2 | 1 |
| 35. 我感到不合适                    | 1 | 2 | 3 | 4 |
| 36. 我是满足的                     | 4 | 3 | 2 | 1 |
| 37. 一些不重要的思想总缠绕着我，并打扰我        | 1 | 2 | 3 | 4 |
| 38. 我产生的沮丧是如此强烈，以致我不能从思想中排除它们 | 1 | 2 | 3 | 4 |
| 39. 我是一个镇定的人                  | 4 | 3 | 2 | 1 |
| 40. 当我考虑我目前的事情和利益时，我就陷人紧张状态   | 1 | 2 | 3 | 4 |

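### Both trait-anxiety forms in Appendix D print the state scale's intensity answers, whereas section 3.4.2 defines the trait score on frequency answers

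*Protocol*

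**What the plan says.** Section 3.4.2 gives the two subscales different answer scales. For the state scale, the four points run upward in strength from a complete absence of the feeling: "all, 2 means some, 3 means moderate, and 4 means very obvious". For the trait scale they run upward in frequency: "In T-AI, 1 means almost none, 2 means some, 3 means often, 4 means almost always". This agrees with the stated purpose of the trait scale, "which is used to assess individual frequent emotional experiences". The same section gives each subscale total a minimum of 20 and a maximum of 80.

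Appendix D holds the forms that participants fill in. The English trait form (Form Y-2) is headed "Not at all | Somew hat | Moderat ely so | Very much so" and the English state form (Form Y-1) "Not at all | Somewhat | Moderately so | Very much so". The Chinese trait form is headed "完全 没有 | 有些 | 中等 程度 | 非常 明显", which are intensity labels again and the same as those on the Chinese state form. The English trait instruction asks the participant "to indicate how you generally feel", and the Chinese one likewise asks about usual feelings.

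Section 3.6 lists anxiety, with depression, as a tertiary outcome.

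**The concern.** The four answer labels are part of the measurement. How often a feeling occurs and how strong it is are different quantities, and a mild feeling that is nearly always present would be placed differently on the two scales. If the forms are used as printed, every trait item is answered by strength, while the protocol tells the reader that the score records frequency.

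Section 3.4.2 presents the inventory as a way to separate passing anxiety from a stable tendency. In the protocol's own description, two features separate the subscales: the time frame in the instruction and the answer scale. The printed forms keep the first and lose the second. At stake are the meaning of the reported trait total and its link to the psychometric figures quoted in support of it.

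**Working it through.** No sample size, power or error rate enters this point. The check is to set the definition in section 3.4.2 beside the headings of the four forms in Appendix D.

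| Form | Scale type defined in 3.4.2 | Scale type printed in Appendix D | Match |
|---|---|---|---|
| State, English | intensity | intensity | yes |
| State, Chinese | intensity | intensity | yes |
| Trait, English | frequency | intensity | no |
| Trait, Chinese | frequency | intensity | no |

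The state forms match in 2 of 2 versions and the trait forms in 0 of 2. No frequency heading appears on either trait form.

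**Could it be an artefact of reading the PDF?** This is not plausible. The headings are complete and legible, apart from words broken across lines in the English trait form. The same substitution occurs in two separately laid-out language versions. A damaged table would not turn four frequency labels into four coherent intensity labels twice.

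**How many items are affected?** The English trait form numbers its items 21 to 30, then a second 30, then 31 to 33 and 35 to 40: 10 + 1 + 3 + 6 = 20. The Chinese form runs from 21 to 40, also 20. This is the whole trait subscale, half of the 40 items in the inventory.

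**Would the data reveal it?** The lowest total is 20 × 1 = 20 and the highest is 20 × 4 = 80. Both agree with the range in section 3.4.2 and both hold under either set of labels. A range check would pass.

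**When is the form used?** Section 3.3.2 places the inventory at pre-test1 and post-test2, in both groups. The single-session study has only the Stroop test and heart rate variability. The mismatch therefore touches both arms and both tests of the 12-week comparison, and nothing in the single-session study.

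**The case against.** The strongest reply is that little follows from the mismatch, and much of that reply stands. The instruction on the trait form keeps the general time frame, while the state form asks about the present moment, so the two subscales are still told apart. Both arms answer the same form at both tests, so the group-by-time comparison is not biased by the labels alone. Anxiety is tertiary, and section 3.6 names no trait-specific outcome or hypothesis. The sample size does not depend on it.

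A reader might go further than the documents allow in four ways.

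- **That a short-lived calming effect would be reported as a change in trait anxiety.** The inventory is not given around a Tai Chi session. It is given 2-3 days before the intervention and within 2-3 days after the 12 weeks, and it comes with the depression scale at the start of the test order. Nothing in the protocol shows that trait answers would drift towards present feeling.
- **That the error is worth a certain number of points per item.** Such figures can come only from imagined respondents, whose errors may run in opposite directions. The protocol gives no basis for a size.
- **That the quoted trait alpha of 0.781 is known not to apply.** Section 3.4.2 gives the coefficient and a citation, but not the answer labels behind it. The most that can be said is that it cannot be assumed to hold for a form that departs from the protocol's own definition.
- **That a score from the printed form may not be reported as trait anxiety at all.** Stating the labels that participants saw is enough.

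None of this removes the contradiction between the section and its appendix.

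**Conclusion.** The point holds as an inconsistency between the definition of the instrument and the instrument itself. As printed, the trait form yields a 20-item intensity rating of general feelings, which is not the frequency-based trait score that section 3.4.2 defines. It affects the whole trait total, in both arms and at both tests, in both language versions. It is not a source of bias between arms, and its effect on scores cannot be quantified from the protocol.

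The conclusion assumes that the Appendix D forms are the ones handed to participants, and that section 3.4.2 states the intended definition. The second assumption is supported by that section's own description of what the trait scale is for. The matter should be corrected because the correction is nearly free and the data would not expose the problem later. It does not threaten the primary analysis.

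**What to change.** Before pre-test1, replace the four answer headings over items 21-40 in Appendix D, in English and in Chinese, with the four frequency answers that section 3.4.2 already gives for the trait scale. The answer headings of the state form need no change.

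This concerns the headings only. The scoring printed beside individual items is a separate matter. For example, the first state item, on feeling calm, is printed without reversal, although section 3.4.2 says all positive items are reversed. New headings would not settle that, and it is sensible to check it in the same revision.

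If any form has already been completed, keep the same form at both tests so that pre and post remain comparable. Report the answer labels actually shown and note the departure from section 3.4.2.

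The cost is reprinting the trait form in two languages. The schedule, sample size and analysis do not change.
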